## Abstract

**Background:**

Inadequate patient engagement in care is a major barrier to successful transitions from the inpatient setting and can lead to preventable adverse events after discharge, particularly for older adults. While older adults may be less familiar with mobile devices and applications, they may benefit from focused bedside training to engage them in using their Personal Health Record (PHR). Mobile technologies such as tablet computers can be used in the hospital to help bridge this gap in experience by teaching older, hospitalized patients to actively manage their medication list through their PHR during hospitalization and continue to use their PHR for other post-discharge tasks such as scheduling follow-up appointments, viewing test results, and communicating with providers. Bridging this gap is especially important for older, hospitalized adults as they are at higher risk than younger populations for low engagement in transitions of care and poor outcomes such as readmission. Greater understanding of the advantages and limitations of mobile devices for older adults may be important for improving transitions of care.

**Objective:**

To better understand the effective use of mobile technologies to improve transitions in care for hospitalized, older adults and leverage these technologies to improve inpatient and postdischarge care for older adults.

**Methods:**

We will compare an intervention group with tablet-based training to engage effectively with their PHR to a control group also receiving tablets and basic access to their PHR but no additional training on how to engage with their PHR.

**Results:**

Patient enrollment is ongoing.

**Conclusions:**

Through this grant, we will further develop our preliminary dataset and practical experience with these mobile technologies to catalyze patient engagement during hospitalization.

**ClinicalTrial:**

ClinicalTrials.gov NCT02109601; https://clinicaltrials.gov/ct2/show/NCT02109601 (Archived by WebCite at http://www.webcitation.org/6jpXjkwM8)

## Introduction

### Engagement in Hospital Care and Personal Health Records

Low engagement in discharge planning and poor understanding of discharge medications are major barriers to promoting successful transitions of care for older adults at many US hospitals. As many as 1 in 5 older patients experience an adverse event after discharge, many of which are likely preventable [1-3]. The overall impact of these poor transitions on costs and outcomes of care is also substantial: 15% to 30% of Medicare patients experience unplanned readmissions with related cost exceeding $17 billion annually [4]. Accordingly, a new Medicare policy to reduce readmission rates was introduced as a core cost-saving component of the Affordable Care Act in 2012, and many hospitals have initiated intense efforts to improve transitions of care [5,6]. Many hospitals have deployed discharge coordinators and extended discharge training for hospital staff to improve transitions, but uses of mobile technologies to add or extend the value of these human interventions have been understudied [7,8].

Many existing technology-enabled interventions have relied heavily on provider uses of the electronic medical record (EMR) to increase the completion and accuracy of key transition tasks such as scheduling appointments, communicating with providers, and completing medication reconciliation [9-11]. While EMR-based interventions have been successful in reducing preventable adverse drug events from inaccurate medication reconciliation, they are clinician-centered and do not actively engage patients. This is a missed opportunity not only to enhance patients’ understanding of their medication list but also to learn about using their personal health record (PHR) to continue actively monitoring their medication list after discharge. Furthermore, interventions focused only on medication reconciliation do not address other important aspects of care transitions such as managing follow-up appointments, viewing test results, and communicating with providers. An ideal patient-centered mobile health intervention would facilitate patients’ ability to view and interact with their medication list as well as empower patients to engage in these other aspects of postdischarge care through active use of their PHR.

### Mobile Technology, Hospital Care, and Older Adults

The widespread use of mobile computers (laptops, tablets, and smartphones) in everyday activities has prompted surprisingly few studies of mobile devices in the care of hospitalized patients. Health care provider use of tablet computers to collect clinical registration data, distribute educational materials to patients, or do clinical work (eg, check labs, write notes) has been studied primarily in outpatient settings [12-17]. To date, however, there are very few studies of tablet use by *patients* in the *inpatient* setting, and none have focused on challenges specific to older, hospitalized adults [18]. To address these knowledge gaps, we propose two aims that will create data needed to assess advantages and limitations of these devices and develop a preliminary dataset and practical experience to build and scale innovative approaches to patient engagement during hospitalization.

### Study Aims and Project Impact on Patient Care

We propose a structured, tablet-based intervention targeted to older patients (aged 50 years or more) admitted to the medical service to enhance PHR use in both inpatient and postdischarge settings for specific tasks. All participants will receive study tablets and access to their PHR. Intervention patients will receive additional training related to using their PHR for specific tasks such as medication management, making appointments, viewing test results, and communicating with providers.

#### Aim 1: To Promote Inpatient Engagement With Their PHR During and After Hospitalization.

We will analyze patients’ use of their PHR throughout hospitalization and also for 7 days after discharge to determine if our intervention affects likelihood of PHR use to view medications, check lab results, view appointments, or send a provider message.

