### Randomization and Intervention

To randomize patients into intervention and control groups, we used an Internet-based coin toss random number generator (Random.org). The research assistant performs this randomization process after patient screening and consent. If the result of the coin toss is heads, the patient is enrolled in the intervention arm; if the result is tails, the patient is enrolled in the control arm. Patients were enrolled Monday through Friday only, no weekends or holidays.

Our project will provide all study participants with tablets and access codes to MyChart while they are hospitalized. Intervention patients will also receive bedside training from study research assistants on key functions of MyChart including how to view medication lists (see Multimedia Appendix 1). Through our preliminary work, we have created a semistructured tutorial for this bedside training that assistants can administer to patients. While this tutorial allows for a basic level of content uniformity for all patients, it is flexible enough to allow assistants to speed up or slow down or otherwise tailor the depth of explanation to the needs of each individual patient (see Multimedia Appendix 2). This study was approved by the UCSF Institutional Review Board and registered at Clinicaltrials.gov [NCT02109601].

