### Data Collection and Sources of Data

After creating a list of eligible patients, research assistants will approach medical teams during rounds (9:00 AM to 11:00 AM) to ensure that screened patients do not have exclusion criteria (Figure 1). The assistants will then approach patients to explain the study, including basic instructions for tablet use (on/off, opening/closing applications, and typing with touchscreen); intervention patients only will receive additional instruction in the form of the semistructured tutorial. The assistant will then leave the device with the patient and return to recollect it after about 4 to 5 hours. The assistant will perform a debrief interveiw upon return and ask patients to view and verify their preadmission medications using the medication list in their PHR. Success (gross pass/fail) in this task will be defined as patient ability to independently log in, locate their medication list, and verify their prehospitalization prescriptions (MyChart does not show inpatient medications unless they are continued at discharge). We will not require patients to correctly describe indications for every medication to receive credit; they will only be asked to identify which medications are familiar to them and which are not. We will use frequency analysis to compare the percentage of intervention group who are able to complete this task with the control group.

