Sources of data will include surveys that will be administered on the device, semistructured debrief interviews administered by assistants, and data on postdischarge access to the PHR from our EMR data repositories. All patients will answer basic questions about demographics, health literacy, and technology use in a preuse survey. The postuse survey will ask about satisfaction with the device to access their PHR and any technical issues. We have developed an interview tool for assistants to use to collect information about patient-reported problems with devices and ask open-ended questions about the overall experience using the tablet. During the debrief interview, the assistant will also ask the patient to demonstrate ability to access their PHR to view and verify their preadmission medications using their PHR medication list. Data about patient use of their PHR is compiled by our EMR in a searchable database (Clarity). We will query Clarity at 7 days to determine access and specific PHR tasks accomplished by all patients both during their hospital stay and for 7 days after discharge. We will also use the Clarity database to identify our virtual cohort of patients who were already engaged with their PHR (1 or more log-ins in the month prior to hospitalization) and were hospitalized during the same 12-month period of our study.

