### Data Analysis

Our overall objective is to assess whether inpatients can successfully use iPads for clinically useful tasks such as viewing their medications or labs or messaging their providers by using their PHR. First, we will assess this overall goal using descriptive statistics (frequency analysis) to describe time required to orient patients to tablets and basic use metrics for PHR (time spent using PHR, number of PHR tasks observed by assistant, etc). Next, we will determine the total number of log-ins to the PHR and number of clicks on different domains of the PHR (medications, labs, appointments) by querying the PHR database. We will extract basic information about whether each patient has accessed their PHR (successful log-in), when they first logged in (time from discharge), and how many times they logged in. Additionally, we will extract information about specific tasks accomplished at any point during both inpatient and postdischarge periods. We will use frequency analysis to compare the following for intervention versus control patients: rates of PHR access, time to first log-in, total number of log-ins, and number of specific tasks (refill prescription, make/change appointment, view test result, or send message to provider) accomplished within 7 days. Finally, we will assess patient satisfaction with devices overall and PHR use specifically. We will perform bivariate analyses (chi-square tests) to determine whether ability to perform key PHR tasks (eg, view medications or lab results) vary according to demographics such as age, gender, health literacy, or technology usage (eg, types of devices owned, frequency of Internet use). Although most of our findings will be descriptive, we plan to enroll 100 patients to enable detection of a 10% difference in ability to perform a key inpatient task (medication verification) and one of several key postdischarge PHR tasks (80% power, 2-sided alpha 0.05).

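### Inpatient PHR use is counted over the whole hospital stay, so use before randomization enters the Aim 1 outcome and can weaken the comparison between arms

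*Protocol article*

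**What the plan says.** Three places in the protocol article describe the inpatient period, and none gives it a start later than admission.

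- Introduction, Aim 1: the analysis covers "use of their PHR throughout hospitalization and also for 7 days after discharge".
- Methods, Data Collection and Sources of Data: the Clarity query is to determine access and "PHR tasks accomplished by all patients both during their hospital stay and for 7 days after discharge".
- Methods, Data Analysis: the extraction takes "specific tasks accomplished at any point during both inpatient and postdischarge periods".

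Table 2 reports inpatient use for the whole hospitalization, under one heading for participants and for the virtual cohort.

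On timing, Randomization and Intervention states: "The research assistant performs this randomization process after patient screening and consent". It adds: "Patients were enrolled Monday through Friday only, no weekends or holidays". Study Design, Participants, and Setting says that assistants screen each morning for new patients, and that the PHR opens in ordinary browsers on phones and computers as well as tablets. Table 2 lists 22 participants (given as 50%) with previous PHR experience.

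**The concern.** Randomization falls inside the outcome window. A patient who already has PHR access can log in on a personal device after admission and before being approached. Under the wording of Aim 1 that use belongs to the inpatient outcome of whichever arm the patient later joins, yet allocation cannot have changed it.

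The hypothesis at stake is that trained patients are more likely than controls to use the PHR while in hospital. Use that is fixed before allocation raises the proportion of users in both arms and leaves less room for a difference. The article itself calls the study relatively small, so avoidable attenuation matters.

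**Working it through.** The plan gives no figure for use before randomization, so there is nothing to reproduce on this point. The sample-size statement concerns other outcomes, and the argument does not rest on it.

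**Inputs from the article:** mean stay 5.79 days (Table 2, study group); 100 patients, so about 50 per arm; two-sided alpha 0.05; 22 participants with previous PHR experience.

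**Assumed:** q, the share of patients who use the PHR between admission and randomization; the use rates after randomization; the day of enrolment.

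**Any inpatient use.** Let p be the probability of use after randomization. With q equal in both arms and independent of later use:

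- P(any use in stay) = 1 − (1 − q)(1 − p)
- Difference between arms = (1 − q) × (p_training − p_control)

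For a true 20-point difference:

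- q = 0.1: 0.9 × 20 = 18 points
- q = 0.3: 0.7 × 20 = 14 points

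If only patients with previous experience contribute, about half the sample, these values of q mean that 0.1/0.5 = 20% and 0.3/0.5 = 60% of them logged in before enrolment.

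Power with 50 per arm, pooled-variance two-proportion test, assumed rates 50% and 75% after randomization:

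| q | Rates over whole stay | Difference | Power |
|---|---|---|---|
| 0 | 50.0% vs 75.0% | 25.0 points | 74% |
| 0.1 | 55.0% vs 77.5% | 22.5 points | 67% |
| 0.2 | 60.0% vs 80.0% | 20.0 points | 59% |
| 0.3 | 65.0% vs 82.5% | 17.5 points | 51% |

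Independence matters here. In general, the whole-stay count discards q times the training effect among early users. If early users would mostly log in again whatever the arm, that effect is small and the loss is smaller than the table shows.

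**Counts.** If a patient uses the PHR evenly over the stay and a share f of it precedes randomization, a true rate ratio of 1.5 is observed as f + 1.5(1 − f):

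- 1 day: f = 1/5.79 = 0.17, observed ratio 1.41
- 2 days: f = 2/5.79 = 0.35, observed ratio 1.33
- 3 days: f = 3/5.79 = 0.52, observed ratio 1.24

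This applies to patients able to use the PHR from admission; over the whole sample the effect is smaller. The difference in mean counts is unchanged in expectation, but early use can add variance to it.

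**The case against.** The strongest reply is that the article never says outright that use before consent is an outcome. The Clarity and Data Analysis sentences describe what will be extracted, and a condensed article may leave the exact start of a window to fuller documents. That limits the certainty. However, the article does state a window, three times and consistently, and the stated window includes the time before randomization.

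Several stronger readings are tempting and are not supported.

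- **That the trial is biased towards the training arm.** Use before randomization is balanced in expectation. Chance imbalance is possible with about 50 per arm, but it has no preferred direction.
- **That an early user is already a success on every listed arm comparison.** The list in Data Analysis ends with a seven-day limit, and first log-in is timed from discharge. On a natural reading at least the task counts there are postdischarge. The inpatient contrast rests mainly on Aim 1 and its hypothesis.
- **That patients wait several days.** Screening each morning for new patients points to a short lag except over weekends and holidays. The 2-day and 3-day rows are illustrations only.
- **That the short tablet loan measures the problem.** The device is collected after about 4 to 5 hours, 4/(5.79 × 24) = 2.9% to 5/(5.79 × 24) = 3.6% of a mean stay. But both arms receive it, and training is meant to influence later use on any device. Time after the tablet is returned is legitimate outcome time.
- **That Aim 2 flatters the programme.** Both groups are counted over the whole stay. All 400 virtual-cohort patients are prior users, so early use may favour the cohort, and Table 3 adjusts for length of stay and prior experience.

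Previous PHR experience also does not prove current use, so q could be small.

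**Conclusion.** The point holds for the inpatient PHR-use comparison in Aim 1. As written, the window includes time in which allocation cannot act. The consequence is attenuation and noise, not bias towards either arm. Under independence a 20-point difference in any use falls to 18 points at q = 0.1 and to 14 at q = 0.3. The true size cannot be fixed, because neither q nor the time from admission to enrolment is given, and the loss shrinks if early users respond less to training.

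The outcomes in the sample-size statement, medication verification at debrief and postdischarge PHR tasks, are untouched. For Aim 2 the common window is acceptable; what needs care is attributing study-group use before enrolment to the tablet programme. The change is worthwhile because it removes an avoidable loss at little cost.

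**What to change.** For the randomized comparison, define inpatient PHR use as use from randomization (or tablet hand-over, the same choice in both arms) to discharge. Take log-ins from admission to randomization as a baseline covariate, not as outcome.

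For Aim 2, keep the whole-stay window for both groups, and state that study-group use before enrolment is not credited to the tablet or the assistance. Counting the virtual cohort from a hospital day matched to the enrolment days is an optional sensitivity analysis.

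The plan already extracts the timing of first log-in and separates inpatient from postdischarge use, so Clarity should hold the times needed. The change also assumes that the time of randomization or hand-over is recorded. The cost is a small change to the query and the outcome definition, and slightly lower inpatient counts. No further patient contact is needed.

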#### Aim 2: To Compare Effects of an Inpatient PHR Engagement Intervention to a Virtual Cohort.

We will compare PHR engagement of our study participants to a virtual cohort of patients who were hospitalized but who were already regular users of their PHR. Patients in this virtual cohort will be identified through review of EMR data only and receive no intervention—they will serve as a benchmark for all participants (both intervention and control) in our study.

We hypothesize that those in the intervention group will be more likely than the control group to use their PHR while they are inpatients and after discharge and that patients in both the intervention and control groups will be more likely to use their PHR in these settings than the virtual cohort. In addition to testing these hypotheses, our project is designed to have significant impact on patient engagement with their care during hospitalization at our hospital. We will also add significant value to existing efforts by our health system to increase patient use of existing technologies: our system uses the PHR application called MyChart (Epic Systems Corp), a Web-based patient portal that allows patients to access to their PHR and perform health care tasks such as sending messages to providers, requesting appointments, viewing test results, and reviewing their medications. The overall objective of this research is to study the use of mobile platforms to improve transitions in care for older, hospitalized adults.

## Methods

### Study Design, Participants, and Setting

This is a prospective, randomized interventional study of tablet computers (iPad 16 GB 3^rd^ generation Model A1430) as a new platform to engage older patients in actively using their PHR during and after hospitalization. We focused on tablet computers because they are light and mobile, which is helpful in the inpatient setting (eg, patients laying in gurneys for hours, patients with limited strength). The PHR used at our institution is mobile-friendly and easily accessible via Web browsers commonly used on tablets, desktops, laptops, and smartphones. We plan to enroll 100 hospitalized patients over 12 months on two general medical units at a large, academic teaching hospital (University of California, San Francisco [UCSF] Medical Center). We will also leverage EMR data to compare these 100 patients to a virtual cohort of 400 patients with the same inclusion/exclusion criteria who were already engaged in PHR use; patients in this virtual cohort will have no direct involvement in the study and will serve only as a benchmark for engagement by the 100 patients who actively participate in the study.

Each morning, research assistants will screen for new patients through UCSF’s electronic medical records by searching for medical service. While our study focus is on older patients (aged 50 years or more), we will also enroll patients younger than 50 years in order to compare and contrast patterns of use between these groups. We will include adult, English-speaking, cognitively intact patients on the medical service. To ensure patients selected will be able to use the iPad, we will exclude patients who are reported by the medical team to be cognitively impaired, blind, deaf, or involuntarily hospitalized because of mental illness. We will also exclude those who are unable to understand the study and consent to participation or who are otherwise excluded at the discretion of their medical team.

### Randomization and Intervention

To randomize patients into intervention and control groups, we used an Internet-based coin toss random number generator (Random.org). The research assistant performs this randomization process after patient screening and consent. If the result of the coin toss is heads, the patient is enrolled in the intervention arm; if the result is tails, the patient is enrolled in the control arm. Patients were enrolled Monday through Friday only, no weekends or holidays.

Our project will provide all study participants with tablets and access codes to MyChart while they are hospitalized. Intervention patients will also receive bedside training from study research assistants on key functions of MyChart including how to view medication lists (see Multimedia Appendix 1). Through our preliminary work, we have created a semistructured tutorial for this bedside training that assistants can administer to patients. While this tutorial allows for a basic level of content uniformity for all patients, it is flexible enough to allow assistants to speed up or slow down or otherwise tailor the depth of explanation to the needs of each individual patient (see Multimedia Appendix 2). This study was approved by the UCSF Institutional Review Board and registered at Clinicaltrials.gov [NCT02109601].

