## Results

Preliminary data from our protocol are show in Table 1. To date, we have enrolled 45 patients; approximately half our sample comprises older adults (50-79 years, 22) and about half (24) are female. Most participants reported owning a laptop computer (34, 75%) or smartphone (29, 64%); desktop and tablet computer ownership were lower at 54% (24) and 51% (23), respectively. A strong majority of patients (39, 86%) indicated they access the Internet daily. While 82% (37) reported looking up health information for themselves on the Internet in the past 12 months, only slightly more than half (27, 59%) had used the Internet to communicate with a health care provider and few had used it to schedule a medical appointment (18, 40%) or refill a prescription (17, 37%).

**Table 1 table1:** Participant characteristics (n=45).

		n (%)
Age (years)	
	18-39	9 (19)
	30-49	14 (32)
	50-79	22 (49)
Gender	
	Female	24 (53)
	Male	19 (42)
	Declined/no response	2 (4)
Device ownership	
	Desktop computer	24 (54)
	Laptop computer	34 (75)
	Smartphone	29 (64)
	Tablet computer	23 (51)
Internet use	
	Daily	39 (86)
	Several times a week	3 (6)
	Once a week or less	1 (3)
Prestudy online health tasks	
	Looked up health information	37 (82)
	Communicated with provider	27 (59)
	Scheduled medical appointment	18 (40)
	Refilled prescription	17 (37)
Orientation to iPad	
	Required 15 minutes or less	36 (81)
	Required 16 to 30 minutes	4 (9)
	Required 30 minutes or more	5 (10)
Independently access/navigate PHR on iPad	
	Log in/verify info	28 (62)
	Medications list page	34 (76)
	Medications refills page	18 (40)
	Scheduled appointments page	38 (85)
	Test results page	38 (85)
	Secure messaging page	37 (82)

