### Conclusions

We have designed a protocol to examine whether the provision of tablet computers and varying levels of PHR assistance (log-in only for control, extensive guidance for intervention) can improve inpatient use of their PHR to engage in hospital care. Our preliminary results suggest that learning about the device is not a significant barrier and that all patients actively enrolled (intervention and control) use their PHR at rates similar to a passively enrolled virtual cohort of patients who were already engaged with their PHR. Our final results will examine whether the intervention patients are different than control patients in terms of inpatient and postdischarge use of their PHR or whether the mere provision of tablets and log-in assistance in the hospital might be enough to explain higher PHR engagement in these patients. Our results are designed to have real-world impact at our medical center and may have important applications for many other medical centers and health systems that are searching for effective implementation strategies to increase patient engagement with PHR systems already in use in their facilities.

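### The key inpatient pass/fail outcome is judged by the unmasked research assistants who allocate and train patients, and no reported item is identified as that outcome

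*Protocol article*

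**What the plan says.** **Allocation.** Under Randomization and Intervention, "we used an Internet-based coin toss random number generator (Random.org") is the source of the assignment, and "The research assistant performs this randomization process after patient screening and consent".

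**Training.** The same section states that "Intervention patients will also receive bedside training from study research assistants on key functions of MyChart". The tutorial is semistructured, and "it is flexible enough to allow assistants to speed up or slow down or otherwise tailor the depth of explanation".

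**Scoring.** Under Data Collection and Sources of Data, the assistant leaves the tablet, returns after about 4 to 5 hours and conducts the debrief in which the patient is asked to do the medication task. Success is a gross pass or fail and "will be defined as patient ability to independently log in, locate their medication list, and verify their prehospitalization prescriptions".

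**Weight of the outcome.** Data Analysis names medication verification as the key inpatient task for which 100 patients are enrolled, with a target difference of 10%.

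**Log-in help.** "Our project will provide all study participants with tablets and access codes to MyChart while they are hospitalized". Principal Findings says that everyone had assistance logging in, and Conclusions describes "varying levels of PHR assistance (log-in only for control, extensive guidance for intervention").

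**Interim figures.** Table 1, under "Independently access/navigate PHR on iPad", gives 28 (62%) for the log-in row and 34 (76%) for the medications list page, both arms together, n=45.

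**The concern.** One staff group learns the assignment, delivers the intervention at a depth it chooses, and then decides whether the patient passed. The outcome depends on a word, independently, that leaves room for judgement: a hint or a prompt may or may not count as help. An assessor who knows the arm can apply that word more generously to trained patients without meaning to. The article describes nothing that would prevent this.

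At stake is the one inpatient comparison that the sample-size statement names. A difference there could reflect scoring instead of training.

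A second, smaller problem is that the interim results report steps of the task, not the task as defined. A reader cannot tell which reported figure, if any, is the success rate.

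**Working it through.** **1. Who knows the arm.** Assistants toss the coin, and only intervention patients get the tutorial from assistants. Assistants run the debrief. If the trainer debriefs, the arm is known with certainty. If a colleague debriefs, nothing described keeps the arm from that colleague.

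**2. How many judgements matter.** Inputs: 100 patients and a 10-point target (Data Analysis), and about 50 per arm expected from a fair coin.

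0.10 × 50 = 5 patients.

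**3. What a scoring shift would do.** The documents give no size for such a shift, so it is assumed and shown as a range. The calculation is an exact enumeration of the uncorrected chi-square test at two-sided 0.05, with 50 per arm and no true difference. Passes in the intervention arm are shifted upward. True success rates of 62% and 76% are borrowed from Table 1.

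| Assumed shift | Patients of 50 | Rejection rate, true rate 62% | Rejection rate, true rate 76% |
|---|---|---|---|
| 0 points | 0 | 5.1% | 5.1% |
| 5 points | 2.5 | 8.1% | 9.5% |
| 10 points | 5 | 18.4% | 25.3% |
| 15 points | 7.5 | 37.1% | 55.3% |

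For scale, at a true rate of 62% an arm of 50 has 0.38 × 50 = 19 true failures, so a 10-point shift means passing 5/19 = 26% of them. At 76% there are 0.24 × 50 = 12, and 5/12 = 42%. If only 10% of true failures were passed, the rejection rate would rise to just 6.8% (true rate 62%) or 6.0% (76%).

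**4. Table 1 against the definition.** The printed percentages reproduce: 28/45 = 62.2% and 34/45 = 75.6%.

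The definition requires log-in and list located and list verified. If the log-in row means independent log-in:

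- success is at most min(28, 34) = 28, or 28/45 = 62%;
- at least 34 − 28 = 6 patients reached the list without an independent log-in;
- the number with both steps is at least 28 + 34 − 45 = 17, or 38%. Full success could be lower still if verification is a further step.

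The bound is conditional. The row label also mentions verifying information, so it may be a joint item. If that information is something other than the medication list, the number who logged in unaided could exceed 28.

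**5. Which outcomes are exposed.** Log-ins and clicks during the stay and for 7 days after discharge come from Clarity, so no assistant scores them.

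The 10-point target serves here only as a yardstick. Whether 100 patients can detect it is a separate matter.

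**The case against.** The strongest reply is that this is a condensed article. Multimedia Appendices 1 and 2, listed as protocol details and an example of the debrief tool, are not at hand and may hold a scoring form and allocation details. That stands for the absence of a form or log. It does not remove what the article itself states: the staff who train also score, and the rule is a coarse pass or fail.

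Several stronger readings are tempting but are not supported:

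- **One person does everything.** The text names a role, sometimes in the plural. It does not say that one individual tosses, trains and scores for a given patient.
- **Table 1 holds two incompatible success rates.** It lists separate steps, and Results presents the 76% only as viewing the medication list. The two figures can coexist if some patients were helped to log in.
- **The gap between the rows exceeds the target effect.** The roughly 13 points (75.6 − 62.2) separate two different steps pooled over arms. The target is a difference between arms on one task. The first says nothing about differential scoring.
- **Access codes and log-in help contradict each other.** Both can be given. Success is judged at the debrief, hours later, so help at set-up does not by itself decide whether that log-in was independent.
- **The allocation is predictable.** A toss after consent keeps the next assignment unknown. The article describes no safeguard against an unrecorded re-toss, but that is secondary and hypothetical. Chance imbalance under simple randomization is not bias. Permuted blocks would be a preference, and with unmasked staff they could make assignments easier to guess.

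**Conclusion.** The concern holds in a limited form. Unmasked research assistants allocate, train and judge the key inpatient outcome, and five judgements out of 50 equal the target difference. The comparison is open to assessment bias, but the documents do not show that bias has occurred, and no arm comparison has been reported.

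The conclusion assumes about 50 patients per arm and a scorer who knows the arm. The direct statements make the second assumption likely but do not prove it for every patient. The rejection rates illustrate assumed shifts and do not estimate what happened: small leniency does little, while a shift the size of the target raises false rejection to roughly 18% to 25%.

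On the interim figures, neither Table 1 item is labelled as the defined success. If the log-in row means independent log-in, success is at most 62%, and the 76% should not be read as the success rate. The Clarity outcomes are outside this concern.

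**What to change.** For the patients still to be enrolled (100 − 45 = 55 at the time of the article):

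1. Record three items separately at the debrief: logged in without help, list located, list verified. Require all three for success, with one written rule for what counts as help.
2. Check the log-in and medication-tab view against Clarity records from the debrief window. Report the Clarity-only result as a sensitivity analysis, because Clarity cannot show whether someone helped.
3. Where the existing team allows, have an assistant who did not train the patient run the debrief. This reduces knowledge of the arm but does not guarantee masking, since the patient may mention the tutorial.
4. Write down each coin-toss result when it is made.
5. In the final report, label which figure is the defined success and present page-level steps as such.

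The cost is minor scheduling and data-matching work and a possibly lower success rate. Scoring also changes after the first 45 patients, so the change must be dated and documented.
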